## Abstract

INTRICATE is a prospective double-blind placebo-controlled feasibility study, assessing the influence of combined vitamin K2 and vitamin D3 supplementation on micro-calcification in carotid artery disease as imaged by hybrid Sodium [^18^F]Fluoride (Na[^18^F]F) positron emission tomography (PET)/ magnetic resonance imaging (MRI). Arterial calcification is an actively regulated process and results from the imbalance between calcification promoting and inhibiting factors. Considering the recent advancements in medical imaging, ultrasound (US), PET/MRI, and computed tomography (CT) can be used for the selection and stratification of patients with atherosclerosis. Fifty-two subjects with asymptomatic carotid artery disease on at least one side of the neck will be included in the study. At baseline, an Na[^18^F]F PET/MRI and CT examination will be performed. Afterwards, subjects will be randomized (1:1) to a vitamin K (400 µg MK-7/day) and vitamin D3 (80 µg/day) or to placebo. At the 3-month follow-up, subjects will undergo a second Na[^18^F]F PET/MRI and CT scan. The primary endpoint is the change in Na[^18^F]F PET/MRI (baseline vs. after 3 months) in the treatment group as compared to the placebo arm. Secondary endpoints are changes in plaque composition and in blood-biomarkers. The INTRICATE trial bears the potential to open novel avenues for future large scale randomized controlled trials to intervene in the plaque development and micro-calcification progression.

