### 4.3. Statistical Analyses Plan

Our null hypotheses states that MK-7 and vitamin D3 do not influence the change (i.e., progression) of micro-calcifications in 3 months of supplementation when compared to a placebo; there will be no difference in the degree of calcification between the MK7+D3 group vs. the placebo at the end of the study. Our alternative hypothesis states that MK-7 and vitamin D3 have a greater effect on the change of micro-calcification in 3 months of supplementation compared to placebo.

The descriptive statistics for each variable at baseline will be presented for both groups combined and individually (i.e., MK7+D3 and placebo) for each of the following parameters: mean, standard deviation of the variable, standard error of the mean, range (minimum-maximum), median, quartiles, and confidence intervals where necessary. Descriptive statistics for variables at the end of the study will be presented separate for both groups (i.e., MK7+D3 and placebo).

Both intention-to-treat and per protocol analysis will be performed. For the intention-to-treat analysis, all randomized subjects (with data available from the end of the study visit) will be included. In the per protocol analysis, only subjects who fully complied with the prescribed supplementation will be included.

The main outcome parameter (i.e., the longitudinal change time of micro-calcification as measured by the Na[^18^F]F uptake via hybrid PET/MRI) will be presented as a continuous variable. It will be expressed as a mean difference (i.e., the standard uptake value and target-to-background radio of Na[^18^F]F at the end of the study visit minus Na[^18^F]F maximal uptake at baseline). To investigate the existence of significant predictor(s) for the main outcome parameter (i.e., the longitudinal change of micro-calcification), univariate analysis will be used. If the significance level (i.e., α) will be between 5% and 25% at the univariate *t*-test hypothesis testing (i.e., *p* > 0.05 and *p* < 0.25), a multivariate analysis will be used, in order to investigate a possible association or interaction between variables.

In order to decide to either reject or accept our null hypothesis, a two-sided confidence interval using 95% confidence will be calculated and reported. A two-sided hypothesis test using a significance level (i.e., α) of 5% will also be reported.

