The CAC score and the US data will be presented as continuous variables. Their longitudinal change will be also expressed as a mean difference (i.e., value at the end of the study visit minus value at baseline) and will be presented as continuous variables.

For the continuous data including age, blood pressure, body-mass index, lipid-rich necrotic volume, normalized wall index, dp-ucMGP, and other laboratory tests, the distribution of variables will be analyzed (verification of normality of distribution for all subjects) by histograms. To investigate the existence of significant predictor(s) for the secondary outcome parameters, univariate analysis will be used. If the significance level (i.e., α) will be between 5% and 25% at the univariate t-test hypothesis testing (i.e., *p* > 0.05 and *p* < 0.25), a multivariate analysis will be used, in order to investigate a possible association or interaction between variables. If variables display no normal distribution, data will be transformed using appropriate transformations. If transformation is not possible, this data is analyzed by non-parametric statistical tests (i.e., Chi-square test).

Baseline parameters will be presented: sex, age, bodyweight, length, body-mass index, medical history, medication, family history, and cardiovascular risk factors.

Health status and use/changes of medication will be verified during the baseline visit and at the end of the study visit.

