#### 5.2.1. PET Image Evaluation

A certified nuclear medicine physician will evaluate all the PET images, which are corrected for attenuation based on the MRI data, unaware of all clinical information, outcome of the extensive MRI analysis. A dedicated fusion software (Syngovia, Siemens) will be used to analyze the PET images. Mean and maximum standard uptake values (i.e., SUVs) will be normalized for blood tracer activity by dividing them by the mean standard uptake value of blood as measured in the internal jugular vein, the superior vena cava, or the right atrium depending on the vessel wall of interest.

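### The primary outcome formula in section 4.3 names different uptake indices at follow-up and at baseline, and no single PET index is fixed as primary

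*Protocol article*

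**What the plan says.** The abstract names no index: "The primary endpoint is the change in Na[^18^F]F PET/MRI (baseline vs. after 3 months) in the treatment group as compared to the placebo arm". The primary objective in section 4.1 names none either.

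Section 4.3 treats the main outcome as one quantity, "the longitudinal change time of micro-calcification as measured by the Na[^18^F]F uptake via hybrid PET/MRI) will be presented as a continuous variable", and then expresses it as a mean difference: "the standard uptake value and target-to-background radio of Na[^18^F]F at the end of the study visit minus Na[^18^F]F maximal uptake at baseline". The word radio is plainly a slip for ratio and is not the point here.

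Section 5.2.1 shows which indices the image analysis yields, with blood as the reference for the division: "Mean and maximum standard uptake values (i.e., SUVs) will be normalized for blood tracer activity by dividing them by the mean standard uptake value of". So mean and maximum SUV exist, and each has a blood-normalised counterpart.

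For the coronary calcium score and the ultrasound data, section 4.3 writes the change like for like: "value at the end of the study visit minus value at baseline". On testing it says: "A two-sided hypothesis test using a significance level (i.e., α) of 5% will also be reported". It states no division of that 5% among PET indices.

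**The concern.** A change score subtracts a quantity from itself at an earlier time. Here the follow-up term names two quantities without saying mean or maximum. The baseline term names one, a maximum, without saying whether it is divided by blood activity. A TBR and an SUV are on different scales, so a difference between them mixes real change with the conversion from one scale to the other.

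Three things are at stake:

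- **Interpretation within arms.** Section 4.1 asks whether micro-calcification is diminished, halted or reversed. That needs a score whose zero means no change.
- **Precision.** A mismatched difference carries baseline blood activity that a matched TBR difference would remove. The study has 52 subjects.
- **Choice of variable.** With more than one index eligible, the single 5% test has no fixed object. The secondary objective in section 4.2 that relates the primary parameter to the calcium score inherits the same gap.

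**Working it through.** The article gives no SD, effect size or power for this outcome, so there is no stated figure to reproduce. All SUV values, coefficients of variation (CVs) and correlations below are assumptions. Only the formula, the 5% level, the 52 subjects and the 1:1 allocation come from the article.

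**1. Can one reading of the baseline term match both follow-up quantities?**

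| Baseline term read as | Follow-up SUV minus baseline | Follow-up TBR minus baseline |
|---|---|---|
| SUVmax | matches only if the follow-up SUV is the maximum | different scales |
| TBRmax | different scales | matches only if the follow-up TBR is the maximum |

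No single reading matches both. Both match only if the baseline term is silently expanded to the corresponding version of each index.

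**2. No-change check.** Take SUVmax 2.0, SUVmean 1.3 and blood SUV 1.25, identical at both visits, with the baseline term read as SUVmax. A change score must give 0.

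- SUVmax - SUVmax = 2.0 - 2.0 = 0
- SUVmean - SUVmax = 1.3 - 2.0 = -0.70
- TBRmax - SUVmax = 2.0/1.25 - 2.0 = -0.40
- TBRmean - SUVmax = 1.3/1.25 - 2.0 = -0.96

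At blood SUV 0.8, TBRmax - SUVmax = 2.0/0.8 - 2.0 = +0.50. It is 0 only when blood SUV is exactly 1.

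**3. Variance of TBR(end) - SUVmax(baseline) relative to TBR(end) - TBR(baseline).** Write T for TBR, S for SUV and B for blood SUV, with S = T x B, all lognormal. Assume a CV of 25% for the wall signal and 20% for B, scan-to-scan correlation 0.8 (on the log scale) and mean B = 1.0. The result depends on which wall quantity is taken as independent of blood.

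*(a) T (mean 2.0) independent of B.*
- Var(T) = 4 x 0.0625 = 0.250
- Var(S) = 4.25 x 1.04 - 4 = 0.420
- Cov(T1,T0) = Cov(T1,S0) = 4 x (1.0625^0.8 - 1) = 0.199
- Mismatched: 0.250 + 0.420 - 2 x 0.199 = 0.272
- Matched: 2 x (0.250 - 0.199) = 0.102
- Ratio about 2.7

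*(b) S (mean 2.0) independent of B.*
- E(T) = 2 x 1.04 = 2.08
- Var(T) = 4.25 x 1.04^3 - 2.08^2 = 0.454
- Cov(T1,T0) = 4 x 1.0625^0.8 x 1.04^2.8 - 2.08^2 = 0.360
- Cov(T1,S0) = 4 x 1.0625^0.8 x 1.04 - 2 x 2.08 = 0.207
- Mismatched: 0.454 + 0.250 - 2 x 0.207 = 0.291
- Matched: 2 x (0.4543 - 0.3598) = 0.189
- Ratio about 1.5

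Over scan-to-scan correlations 0.6 to 0.9 and mean blood SUV 0.8 to 1.25, simulation gives 1.4 to 6.7 under (a) and 0.98 to 2.8 under (b).

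**4. False-positive rate if k indices were each tested at two-sided 5%.** If independent, 1 - 0.95^2 = 9.75% and 1 - 0.95^4 = 18.55%. Indices from the same scan are correlated. Simulating k equally correlated z-tests (1,000,000 draws) gives:

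| k | correlation 0.5 | correlation 0.9 |
|---|---|---|
| 2 | 9.1% | 7.0% |
| 4 | 15.6% | 9.3% |

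**5. Price of splitting alpha instead.** With 52/2 = 26 per arm, 80% power and no dropout, the detectable difference is (z for alpha + 0.842) x sqrt(2/26). For one index it is (1.960 + 0.842) x 0.277 = 0.78 SD. With a Bonferroni split it is 0.86 SD for two indices and 0.93 SD for four.

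**The case against.** The strongest reply is that this is loose drafting, not a rule anyone would apply literally. The same sentence calls the outcome a longitudinal change, the abstract compares baseline with 3 months, and the like-for-like wording for calcium score and ultrasound suggests the same intent for PET. A sensible analyst would match the indices. That is fair as to intent, but it does not say which index would be matched.

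Four stronger readings are tempting, and the article does not support them.

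- **That the baseline term is certainly an un-normalised SUV, so the score can never be a change.** Section 5.2.1 normalises maximum values too, so the term could mean TBRmax. The offset in steps 2 and 3 applies only to the SUV reading.
- **That the score is negative by construction.** This needs the follow-up SUV to be the mean, which section 4.3 does not say.
- **That there are four primary outcomes and an inflated error rate is built in.** Section 4.3 names two quantities, and section 5.2.1 describes image processing without making anything co-primary. The plan speaks of one outcome and one test, so the error rates are conditional on multiple testing or a late choice.
- **That the treatment comparison is biased, or that more than half of the information is lost.** Randomisation cancels the offset in expectation, and section 4.1 is framed against placebo. The variance loss depends heavily on whether TBR or wall SUV is taken as independent of blood. At one corner of the assumed range there is no loss.

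The feasibility and proof-of-concept label lowers the stakes but does not remove them, because a 5% test and a 95% interval are planned. An unseen analysis plan may settle the matter, but the article prints a formula, and that formula is inconsistent with itself.

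**Conclusion.** The point holds as an inconsistent and incomplete definition of the primary variable. The two terms of the formula do not name the same index, and at least two indices could be reported as the one variable tested at 5%. That much rests on the text alone.

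The sizes rest on assumptions. If the baseline term is un-normalised, the no-change offset for TBRmax minus SUVmax is about +0.5 or -0.4 at mean blood SUV 0.8 or 1.25. The variance is then about 1.5 to 2.7 times that of a matched TBR difference at CVs of 25% and 20%, correlation 0.8 and mean blood SUV 1.0, and about 1.0 to 6.7 times over the wider range. The false-positive rates of 7-9% and 9-16% apply only if two or four indices are each tested at 5%, or one is picked after the data are seen. The between-arm estimate is not biased in expectation. The harm is to within-arm interpretation, usually to precision, and to the pre-specification of the test.

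**What to change.** Before unblinding, restate the primary outcome in section 4.3 as one named index, measured identically at both visits, in the same artery and with the same blood-pool reference. One example is TBRmax at 3 months minus TBRmax at baseline. TBRmax is only an example: any single index matched across visits cures the defect, and nothing in the article favours TBRmax over SUVmax. List the remaining indices as secondary or sensitivity measures, and use the same named index wherever section 4.2 refers to the primary parameter.

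This takes a sentence or two and no new data, because section 5.2.1 already yields every index. The cost is committing to one metric in advance. Keeping several as co-primary with a split alpha is possible, but raises the detectable difference from 0.78 SD to 0.86 or 0.93 SD.

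### The multivariate analysis is called for only when the univariate p-value lies between 0.05 and 0.25, which screens out the strongest predictors and leaves the model for the decision test open

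*Protocol article*

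**What the plan says.** Section 4.3 of the protocol article begins the relevant step with a stated purpose: "To investigate the existence of significant predictor(s) for the main outcome parameter", here the change in tracer uptake over 3 months, by univariate analysis. The condition follows: "If the significance level (i.e., α) will be between 5% and 25% at the univariate" t-test, restated at once in parentheses as p above 0.05 and below 0.25. When it is met, "a multivariate analysis will be used, in order to investigate a possible association or interaction between variables".

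Later in the same section the rule returns for the other endpoints: "To investigate the existence of significant predictor(s) for the secondary outcome parameters, univariate analysis will be used", with the same band, again written both as percentages and as p-values.

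The decision on the null hypothesis has its own paragraph: "In order to decide to either reject or accept our null hypothesis, a two-sided confidence interval using 95% confidence will be calculated and reported". It continues: "A two-sided hypothesis test using a significance level (i.e., α) of 5% will also be reported". That paragraph names no model and does not refer back to the univariate or multivariate step.

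The sample size is in the Abstract: "Fifty-two subjects with asymptomatic carotid artery disease on at least one side of the neck will be included in the study", randomised 1:1.

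**The concern.** A screen for candidate predictors normally has only an upper limit: variables with little sign of association are dropped and the rest are kept. This rule adds a lower limit. A variable with p of 0.05 or less fails the condition, and the section gives no other way into the multivariate analysis. Both bounds are written in two forms, in two places, so a typing slip is unlikely. Because the rule is written out, it is not detail left to a fuller document.

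Two things are at stake. First, the multivariate model would tend to be built from weak or chance associations and to lack the variables that explain most of the outcome. Baseline uptake is a plausible casualty, since it is one component of the change score, although its true correlation with the change is not given. The stenosis group used in the minimization (section 6) is also exposed, since its place in the model would depend on its observed p-value.

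Second, treatment is neither named nor excluded as a screened variable, and the decision paragraph is not tied to a model. A near miss in the unadjusted comparison could therefore open an adjusted analysis that someone later reads as the decisive one.

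**Working it through.** **Inputs from the article.** N = 52, 1:1, so 26 per arm (Abstract); band 0.05 < p < 0.25, two-sided 5% test and 95% interval (section 4.3). **Assumed, because the article gives no values:** the correlation of a predictor with the outcome, the number of covariates, and the share of outcome variance (R²) they explain. All 52 subjects are taken to have outcome data.

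**1. The stated level.** A single unconditional two-sample t-test, 26 per arm, simulated under the null (20,000 trials per scenario), rejects in 4.8% to 5.1% of trials. This agrees with the stated 5%.

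**2. Where the band lies for a predictor.** With n = 52 there are 50 degrees of freedom, and |r| = t / √(t² + 50).
- p = 0.05: t = 2.009, so |r| = 2.009 / √54.03 = 0.273.
- p = 0.25: t = 1.164, so |r| = 1.164 / √51.35 = 0.162.

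Read as an entry rule, a variable qualifies only if its observed |r| lies between 0.162 and 0.273. Anything stronger is left out.

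**3. Chance of qualifying.** Simulated with 40,000 draws per value:

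| True correlation | p < 0.05 (left out) | 0.05 < p < 0.25 (qualifies) | p < 0.25 (upper limit only) |
|---|---|---|---|
| 0 | 5.0% | 20.0% | 24.9% |
| 0.2 | 30.0% | 32.5% | 62.5% |
| 0.3 | 58.6% | 26.2% | 84.9% |
| 0.4 | 85.1% | 11.7% | 96.8% |
| 0.5 | 97.2% | 2.5% | 99.7% |
| 0.6 | 99.8% | 0.2% | 100.0% |

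A check by Fisher's z for a correlation of 0.5: atanh(0.5) = 0.549, standard error 1/√49 = 0.143. The band limits on this scale are 0.164 and 0.280, which lie 2.70 and 1.88 standard errors below 0.549. The probability between them is about 0.030 − 0.003 = 0.026, close to the simulated 2.5%. A variable unrelated to the outcome is thus about eight times as likely to qualify (20.0 / 2.5 = 8).

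**4. If treatment were put through the same rule.** Under the null, the unadjusted p falls in the band in 0.25 − 0.05 = 20% of trials. Count success as unadjusted p < 0.05, or unadjusted p in the band and covariate-adjusted p < 0.05. Simulated with 26 per arm, 1 or 5 covariates, 20,000 trials per scenario:

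| R² of covariates | Type I error, two-step |
|---|---|
| 0 | 5.4% to 6.1% |
| 0.2 | 6.5% to 6.8% |
| 0.4 to 0.6 | 7.0% to 7.1% |

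In the same simulations, one covariate-adjusted analysis fixed in advance, without the gate, rejects in 4.8% to 5.2% of trials.

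**The case against.** The strongest defence is that this is a predictor search, separate from the test of the null hypothesis. The stated purpose is to find predictors and to look at association or interaction, treatment is not named, and the decision has its own paragraph. On that reading there is no second test of treatment and the 5% level stands. This defence holds as far as it goes. A reader might infer that the plan gives a non-significant treatment effect a second chance, or that its 5% level is already lost. The article does not say so. What remains is an ambiguity: treatment is not excluded and the decision model is not named.

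It can also be said that the sentence fixes when a multivariate analysis is run, not which variables enter it. On that reading the exclusion percentages above do not follow directly. But the section then gives no entry rule at all, and a clearly significant univariate result would still lead to no multivariate analysis, which makes no better sense.

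Three further inferences should not be drawn:
- That leaving out strong predictors confounds the treatment comparison. Allocation is randomised, with minimization on stenosis, so the loss is in precision.
- That a t-test cannot be used for continuous predictors such as age. The slope in a univariate regression is tested with a t-test, so the wording is compatible with a valid analysis.
- That calling the p-value a significance level changes the rule. It is loose terminology, and the parenthesis makes the meaning clear.

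Finally, the trial describes itself as a feasibility and proof-of-concept study, and the inflation from one adjusted retest is modest. Both are true and bear on priority. Neither repairs the lower bound.

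**Conclusion.** The rule is wrong as written and should be corrected, though it does not by itself invalidate the primary comparison.

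The firm part is the lower bound. Taken as a screen, it selects against informative variables, and more so the stronger they are. The size depends on assumed correlations and on outcome data for all 52 subjects, but the direction follows from the rule alone. The harm is a misleading predictor model and lost precision, for the main and the secondary outcomes alike.

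The conditional part is the decision test. The rise to about 5.4% to 7.1% needs two things that the article does not state: that treatment passes through the rule, and that the adjusted result counts as success. It also depends on the assumed covariates. If the unadjusted comparison is the only decision test, this part falls away and the first remains.

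**What to change.** In both places in section 4.3:

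1. Delete the lower bound, so that any screen that is kept retains every variable with p < 0.25, including those below 0.05.
2. Label the predictor modelling exploratory, and say that it does not decide the null hypothesis.
3. State that the 95% interval and the 5% test come from one model fixed in advance and reported whatever the univariate p-values are. Treatment with baseline uptake and the stenosis group would be one suitable choice, since the trial already collects both covariates. An unadjusted comparison named in advance would also close the ambiguity.

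The cost is a few lines of wording. No design feature, visit, measurement or sample size changes.

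### Section 4.3 lets a 95% confidence interval lead to accepting the null of no influence, with no margin to justify it and an interval about 0.56 SD wide on each side

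*Protocol article*

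**What the plan says.** All the relevant statements but the sample size are in section 4.3 (Statistical Analyses Plan) of the Protocol article.

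- **Null:** "Our null hypotheses states that MK-7 and vitamin D3 do not influence the change (i.e., progression) of micro-calcifications in 3 months of supplementation", by comparison with placebo.
- **Alternative:** "MK-7 and vitamin D3 have a greater effect on the change of micro-calcification in 3 months of supplementation compared to placebo". No size is attached.
- **Outcome:** the change in tracer uptake from baseline to the end-of-study visit. "It will be expressed as a mean difference".
- **Decision rule:** "In order to decide to either reject or accept our null hypothesis, a two-sided confidence interval using 95% confidence will be calculated and reported".
- **Test:** "A two-sided hypothesis test using a significance level (i.e., α) of 5% will also be reported".

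On size, the Abstract says: "Fifty-two subjects with asymptomatic carotid artery disease on at least one side of the neck will be included in the study", with 1:1 allocation. The intention-to-treat set in section 4.3 is limited to randomised subjects who have end-of-study data.

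The article states no equivalence margin, no smallest relevant difference and no third, inconclusive outcome.

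**The concern.** A confidence interval that includes zero shows that the data are compatible with no difference. It does not show that there is none. Accepting a null of no influence needs an interval narrow enough to exclude every difference that would matter, and hence a stated difference that matters. Section 4.3 offers acceptance as one of two outcomes without that condition.

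The article describes the trial as a feasibility and proof-of-concept study that might open the way to larger trials. A small study of that kind can easily give an interval that covers both no effect and a worthwhile one. Under the rule as worded, such a result falls under acceptance, and the investigators could conclude that the supplements have no influence when the data leave the question open.

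**Working it through.** **Inputs from the documents**

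- 52 subjects, 1:1, so 26 per arm (Abstract).
- Two-sided 95% interval and two-sided 5% test (section 4.3).
- Continuous outcome, end of study minus baseline (section 4.3).

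**Assumptions, because the article gives no figure**

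- The SD of the change score is set to 1, so all results are in units of that SD.
- The comparison of mean change between arms is unadjusted.
- There is no dropout in the main calculation. A case with 42 analysed (21 per arm) is added as a range.
- True effects of 0.5 and 0.8 SD are chosen only for illustration.

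**The plan's own figure.** The total of 52 cannot be reproduced, because the article gives no effect size, SD, power or dropout. Worked backwards, 26 per arm gives 80% power at 0.79 SD (non-central t; 0.78 SD by the normal approximation).

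**Half-width of the interval**

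- Formula: t(0.975, N − 2) × √(2/n).
- 26 per arm: 2.009 × √(2/26) = 2.009 × 0.2774 = 0.557 SD.
- Normal check: 1.96 × 0.2774 = 0.544 SD.
- 21 per arm: 2.021 × √(2/21) = 2.021 × 0.3086 = 0.624 SD.

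**What the interval can exclude when the null is not rejected**

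- Observed difference of zero: the interval runs from −0.56 to +0.56 SD.
- Observed difference just short of significance: the far limit is about 2 × 0.557 = 1.11 SD.

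**How often the rule would end in acceptance when the null is false** (non-central t, two-sided 5%)

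| Assumed true effect | Power, 26 per arm | Not rejected | Power, 21 per arm |
|---|---|---|---|
| 0.5 SD | 42% | 58% | 35% |
| 0.8 SD | 81% | 19% | 72% |

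**Sensitivity to baseline adjustment.** With correlation ρ between baseline and follow-up and equal SDs at both visits, covariate adjustment gives a half-width of 0.557 × √(1 − ρ²) in SDs of the follow-up value. That is 0.48 at ρ = 0.5 and 0.40 at ρ = 0.7. To compare with the figure above, divide by the SD of change, √(2(1 − ρ)):

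- ρ = 0.5: the SD of change is 1.00, so 0.48 / 1.00 = 0.48 SD of change.
- ρ = 0.7: the SD of change is 0.775, so 0.398 / 0.775 = 0.51 SD of change.

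The correlations are assumed. At these values adjustment narrows the interval but leaves it at about half an SD of change.

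**The case against.** The strongest reply is that this is one loose word. The sentence that contains it also commits to reporting the interval, and the next adds a two-sided test. Any non-significant result would appear with its limits, and a reader could see how wide they are. That stands, and it limits the weight of the point. It does not remove it, because the same sentence makes the interval the means of deciding on acceptance.

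Four stronger readings are tempting, and the documents do not support them.

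- **That a non-significant result will be reported as no effect.** Nothing in the article says how such a result will be worded. The rule permits that conclusion but does not prescribe it. Nor is any decision on a larger trial tied to acceptance of the null.
- **That the trial is underpowered.** The article names no target effect, and nothing in it shows that 0.3 or 0.5 SD is the relevant size for tracer uptake. If the full protocol aimed at about 0.8 SD, 26 per arm gives about 81% power. The rule would still be unsound, since failing to detect 0.8 SD does not establish no influence.
- **That the sample-size rationale is missing.** A journal article commonly leaves it to the full protocol, which is not shown here.
- **That a significant harmful result has no reading.** The null is no influence, and a two-sided interval that excludes zero on either side rejects it. A directional expectation with a two-sided test is ordinary practice, and the wording of the alternative does not itself name benefit.

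**Conclusion.** The point holds as a defect in a stated decision rule. Section 4.3 offers acceptance of no influence without a margin, and with 26 per arm the interval reaches about 0.56 SD of change on either side of the estimate (0.62 SD if 42 are analysed). A non-significant result could therefore be concluded as no influence without support from the data.

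The half-width rests on the stated 52 subjects and 1:1 allocation, on complete follow-up and on an unadjusted comparison. The power figures also rest on assumed effects. The logical fault depends on none of these: without a stated margin, no sample size would make an interval that includes zero a ground for acceptance.

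The weight is modest. The estimate, interval, test and significance level are sound as stated; what needs correcting is the conclusion that the rule allows.

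**What to change.** In section 4.3, replace the reject-or-accept wording with reject or fail to reject, and add the reading of a non-significant result. For example:

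> The null hypothesis is rejected if the two-sided 95% confidence interval for the difference in mean change excludes zero. If the interval includes zero, the null hypothesis is not rejected; the result is then inconclusive about it and is interpreted from the interval limits.

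Optional: word the alternative as a difference in change between the arms, to match the two-sided test.

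This does not require naming a margin. If the investigators want to be able to conclude that no relevant effect exists, they would have to prespecify a relevant difference and require the interval to exclude it. That is a substantive decision for which the article gives no figure.

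The cost is an edit to the text, with no change to sample size, procedures or analysis. The downside is that a non-significant result will support only a more cautious conclusion.
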